**Figure 1 F1:**
[figure not shown]
Study design.

#### Interview

Data on self-reported physical activity and secondary outcome measures will be collected during a structured interview, which will be conducted by a trained female interviewer who has a Surinamese, Moroccan or Turkish background. The interviewers are bilingual and can address the questions in the preferred language of the participant. Whenever possible it is tried to send the same interviewer to the participants at all three time points.

During the interview a questionnaire will be used which is constructed to measure self-reported physical activity, motivational factors, subjective and objective health, and health care. Where possible, standard validated questionnaires that have been used previously among non-Western populations will be used [3,10]:

- Self reported physical activity related to travel, house-keeping, work, leisure time, and sports will be measured with the SQUASH, which has been used previously among the Turkish, Moroccan and Surinamese population [3,6,10,26].

- Questionnaires developed for a multi-ethnic population will be used to measure motivational factors related to physical activity: attitudes, social influences, self-efficacy and intention [27-29].

- Perceived health is measured with one item on self-perceived general health with a 5-point likert scale ranging from very good to very poor.

- Common physical complaints are measured such as diabetes, COPD, cardiovascular diseases with the possibility to mention other complaints.

- Well being will be measured with the W-BQ12 (well-being questionnaire)[30].

#### Physical examination (objective health measures)

The physical examination in the intervention and the control group will consist of a standardised measurement of the weight, length, percentage fat, waist and hip circumference. For these measurements the protocol of the SUNSET study will be used [10]. The physical fitness (maximal oxygen uptake) of the women will be monitored through the Siconolfi step test [31]. Briefly, patients will be asked to step up and down a portable bench for three minutes at a rate of 17 steps per minute, which will be kept constant with the help of a metronome. Heart rate will monitored continuously during the test and will recorded at the end of the stage. If target heart rate (65% of the predicted [220 minus age] maximum heart rate) is reached, the protocol will be terminated. Otherwise, a second stage (26 steps per minute) and, eventually, a third stage (34 steps per minute) will be completed with 1 minute of rest between each stage. The steady-state absolute maximal oxygen uptake can be calculated with equations [31].

#### Information on use of health care

We will use the available databases from two health care insurers to obtain data on health care use of the participants. These two companies have confirmed their cooperation.

### Sample Size Calculation

Input for the sample size calculation is derived from a study performed amongst Surinamese (Hindustani and Creole Surinamese) people in the Netherlands (SUNSET study) [10]. The amount of physical activity in this group of women (n = 666) was measured with the SQUASH [26]. From the SUNSET study it appeared that Surinamese women were on the average 1852 (SD: 1100) minutes per week physically active. To be able to detect an absolute difference of 15% in the number of minutes of physical activity per week with an one-sided alpha of 0.05, and a power of 80% 180 women in both groups are needed.

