**Methods:**

The randomized controlled trial will include 360 inactive women from ethnic minority groups, with the majority having a non-Western background, aged between 18 and 65 years old, with regular visits to their general practitioner. Participants will be recruited at healthcare centres within a deprived neighbourhood in the city of The Hague, the Netherlands.

An intervention group of 180 women will participate in an exercise program with weekly exercise sessions during 20 weeks. The control group (n = 180) will be offered care as usual. Measurements will take place at baseline, and after 6 and 12 months. Main outcome measure is minutes of self reported physical activity per week. Secondary outcomes are the mediating motivational factors regarding physical activity, subjective and objective health outcomes (including wellbeing, perceived health, fitness and body size) and use of (primary) health care. Attendance and attrition during the program will be determined.

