### Data Analyses

The main aim of the study is to asses the effect of the intervention on physical activity. Therefore group differences between groups and 95% confidence intervals will be calculated in changes in physical activity after the intervention (between T0 and T1) and in maintenance (T0-T2). The statistical analysis will be performed according to the intention-to-treat principle.

Between group differences will be calculated using the Student t-test for continuous variables or Chi-Square for dichotomous variables. Baseline comparability will be investigated by descriptive statistics to examine whether randomisation was successful. If necessary, adjustments for baseline variables will be performed in the analysis.

Finally, multivariate regression analysis will be conducted to examine the influence of baseline variables and the degree of participation in the intervention on the outcome.

Within the intervention group multivariate regression analysis will be conducted to examine the influence of baseline variables and the degree of participation in the intervention (i.e. the proportion of sessions attended and the components of the intervention followed) on the changes in physical activity.

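### The sample size rests on a one-sided 5% test but the primary outcome is to be reported with 95% confidence intervals, so the stated 80% power does not apply to the planned inference

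*Protocol article*

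**What the plan says.** Sample Size Calculation takes its planning values from an earlier survey, in which "Surinamese women were on the average 1852 (SD: 1100) minutes per week physically active". The target is given as "To be able to detect an absolute difference of 15% in the number of minutes of physical activity per week". The test is planned "with an one-sided alpha of 0.05", "and a power of 80% 180 women in both groups are needed". No reason is given for testing on one side.

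Data Analyses states that "group differences between groups and 95% confidence intervals will be calculated in changes in physical activity", once from baseline to 6 months (T0 to T1) and once, as maintenance, from baseline to 12 months (T0 to T2). It adds: "Between group differences will be calculated using the Student t-test for continuous variables". The sidedness of that test is not stated. Neither a 90% interval nor a one-sided confidence bound is mentioned. Adjustment for baseline variables is foreseen only where the baseline comparison shows a need for it.

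**The concern.** A conventional 95% interval excludes zero in the direction of benefit when a one-sided test is significant at 2.5%. The interval that matches a one-sided 5% test is a 90% interval or a one-sided 95% bound. The two sections therefore imply different evidential standards for the same comparison, and the claimed power belongs to the laxer one.

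Two things are at stake. First, a reader who takes 80% as the chance that the reported interval will exclude zero is misled. Second, a result can fall between the two standards. At the planning SD, a difference of roughly 191 to 227 min/week would be significant one-sided at 5% while the 95% interval still included zero. That band lies not far below the 278 min/week the trial aims to detect, so such a result is realistic, and the article does not say how it would be read.

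**Working it through.** **Inputs.** Mean 1852 and SD 1100 min/week, difference 15%, one-sided alpha 0.05, power 80%, 180 per group (Sample Size Calculation; group sizes also in the abstract). The 95% interval for the difference in change comes from Data Analyses.

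- Difference: 0.15 × 1852 = 277.8 min/week.
- Standardised difference: 277.8 / 1100 = 0.2525.
- Standard error with 180 per group: 1100 × √(2/180) = 115.95 min/week.
- Difference over standard error: 277.8 / 115.95 = 2.396.

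**Step 1: the article's own figure (one-sided 5%).**

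n per group = 2 × (SD/difference)² × (z for alpha + z for power)²
= 2 × (1100/277.8)² × (1.645 + 0.842)² = 193.9, so 194. The t distribution gives 194.6, so 195.

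The stated 180 is not reproduced. Power at 180 is Φ(2.396 − 1.645) = 77.4%, or 77.2% with the t distribution. To give 80% one-sided, 180 per group would need a difference of about 288 min/week or an SD of about 1060.

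**Step 2: the rule implied by a 95% interval (two-sided 5%).**

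- n per group = 2 × (1100/277.8)² × (1.960 + 0.842)² = 246.1, so 247. The t distribution gives 247.1, so 248.
- Power at 180 is Φ(2.396 − 1.960) = 66.9%, or 66.6% with the t distribution.
- The difference detectable with 80% power at 180 per group is about 326 min/week (t distribution), and 326/1852 = 17.6%.

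**Step 3: where the fall from 80% comes from** (t distribution).

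| Source | Power |
|---|---|
| Stated | 80% |
| Recomputed, one-sided 5%, 180 per group | 77.2% |
| Recomputed, two-sided 5%, 180 per group | 66.6% |

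About 2.8 points come from the stated number being short on its own inputs, and about 10.6 points from the change of rule.

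**Step 4: results that fall between the rules.** One-sided 5% threshold: 1.645 × 115.95 = 191 min/week. 95% interval threshold: 1.960 × 115.95 = 227 min/week.

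**Step 5: dependence on the change score.** The SD of 1100 is cross-sectional, but the planned analysis is of change. With equal SDs at both times and baseline/follow-up correlation r, the SD of change is 1100 × √(2(1 − r)), which equals 1100 only at r = 0.5. With baseline adjustment (ANCOVA) the effective SD is 1100 × √(1 − r²). The article gives no r, so the values below are assumptions. Power is two-sided, t distribution, 180 per group.

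| Assumed r | SD of change | Power, change score | Power, ANCOVA |
|---|---|---|---|
| 0.3 | 1302 | 52% | 71% |
| 0.5 | 1100 | 67% | 79% |
| 0.6 | 984 | 76% | 85% |
| 0.7 | 852 | 87% | 92% |

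**The case against.** The strongest reply has three parts.

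*The decision rule is inferred.* Data Analyses says that intervals will be calculated. It does not say that success means excluding zero, and it does not print the word two-sided. A one-sided test reported beside a conventional 95% interval is awkward rather than strictly contradictory, and a condensed article may leave sidedness to the full protocol. This stands in part: two-sided is the conventional reading, not the article's wording. But the article does print a one-sided 5% level in one section and a 95% interval in the other, with nothing to connect them, and the interval is the only inferential standard named for the primary outcome.

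*The 67% depends on an unstated correlation.* This stands. For a change score, two-sided power reaches 80% once the correlation is about 0.64. A reader might take 67% as the power of the planned analysis. The article does not support that, because it gives neither an SD of change nor a correlation.

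*Not all of the shortfall is due to sidedness.* This also stands. A reader might put the whole fall from 80% to 67% down to the mismatch, but step 3 shows that part of it is an arithmetic shortfall already present under the one-sided rule.

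A reader might also infer that the two follow-up times let the trial claim success on either one. The article does not say so: it labels the 12-month comparison as maintenance and states no such rule. The second time point also takes nothing from the 67%, which is power for a single comparison. Nor does the article suggest that anyone means to pick the more favourable of the two standards.

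**Conclusion.** The point holds. The 80% power in Sample Size Calculation does not apply to the inference planned in Data Analyses. At the stated difference and SD, 180 per group gives about 77% power one-sided and about 67% for a two-sided 95% interval; 80% would need about 195 or 247 to 248 per group respectively.

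That the two rules differ, and that two-sided power is the lower, is true whatever the correlation. The size of the power figure is not: 67% requires the SD of the analysed quantity to be 1100, which for change means an assumed correlation of 0.5. The plan's power should therefore be called misstated. The article does not establish that the planned change-score analysis is underpowered, since a correlation above about 0.64 would bring it to 80% two-sided.

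**What to change.** 1. Use one rule in both sections: two-sided 5%, matching the 95% intervals already planned, with the t-test declared two-sided.
2. Restate the power in Sample Size Calculation as about 67% at 180 per group for 277.8 min/week and SD 1100, with a detectable difference at 80% power of about 326 min/week (17.6%). Say that for change scores this assumes a correlation of 0.5, and show the range in step 5 or a sourced correlation. Note that the one-sided calculation gives about 195 per group rather than 180.
3. Prespecify the baseline-adjusted analysis (ANCOVA on baseline physical activity) in place of adjustment only where needed. At an assumed correlation of 0.5 this gives about 79% two-sided power with the same 360 women.

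The cost is wording in two sections and a less favourable stated power. No extra recruitment is required unless the sponsor wants a full 80% without relying on the correlation.

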### Data Analyses

The main aim of the study is to asses the effect of the intervention on physical activity. Therefore group differences between groups and 95% confidence intervals will be calculated in changes in physical activity after the intervention (between T0 and T1) and in maintenance (T0-T2). The statistical analysis will be performed according to the intention-to-treat principle.

Between group differences will be calculated using the Student t-test for continuous variables or Chi-Square for dichotomous variables. Baseline comparability will be investigated by descriptive statistics to examine whether randomisation was successful. If necessary, adjustments for baseline variables will be performed in the analysis.

Finally, multivariate regression analysis will be conducted to examine the influence of baseline variables and the degree of participation in the intervention on the outcome.

Within the intervention group multivariate regression analysis will be conducted to examine the influence of baseline variables and the degree of participation in the intervention (i.e. the proportion of sessions attended and the components of the intervention followed) on the changes in physical activity.

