### Outcome Measures

The primary outcome measure is self-reported physical activity measured in minutes per week. Secondary outcome measures are a) the intention and motivational factors with regard to physical activity (e.g. attitudes, social influences and self-efficacy) b) subjective health outcomes (perceived health and well-being) c) objective health outcomes: fitness of the participants (oxygen uptake) and body size (body mass index, waist-hip ratio and waist circumference, and fat percentage) d) the use of (primary) health care. Furthermore, the participation and the follow-up rate in the study will be assessed as well as the reasons for non-participation or loss to follow-up. Baseline demographic characteristics, such as age, ethnicity, neighbourhood of residence and other socioeconomic factors of potential participants will be recorded.

Attendance during the intake, participation in the weekly sports sessions, and the final evaluation (intervention arm) will be monitored by the lifestyle advisor, who will also notify women prior to the appointment and follow-up with women who have not shown up for a session. In addition, data on the individually tailored content of the intervention and subsequent participation in "Exercise without Prescription" will be registered.

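### The main comparison is a t-test on change scores, with baseline adjustment left to an undefined look at the data; adjustment for baseline SQUASH minutes should be fixed in advance

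*Protocol article*

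**What the plan says.** The Outcome Measures section states: "The primary outcome measure is self-reported physical activity measured in minutes per week". It is measured with the SQUASH questionnaire at T0, T1 and T2 in both arms (Data Collection; Interview).

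Under Data Analyses, group differences with 95% confidence intervals "will be calculated in changes in physical activity after the intervention (between T0 and T1) and in maintenance (T0-T2"). The method is named: "Between group differences will be calculated using the Student t-test for continuous variables". Two sentences then govern adjustment: "Baseline comparability will be investigated by descriptive statistics to examine whether randomisation was successful", followed by "If necessary, adjustments for baseline variables will be performed in the analysis". The section does not say what would make adjustment necessary, which baseline variables would enter, or which result would be primary if both were produced.

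Two regressions follow. One relates the outcome to baseline variables together with degree of participation, which is known only after allocation. The other is confined to the intervention arm. Neither is a baseline-adjusted estimate of the randomised effect.

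**The concern.** There are two problems.

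- **The estimator depends on the data.** The unadjusted change-score difference is the default, and an adjusted one may replace or join it once the baseline table has been seen. With no criterion and no covariate list, the plan does not determine which estimate answers the main question. The article states this rule itself for its main aim, so it is not a detail deferred to another document.
- **The default is the less efficient choice.** A change score subtracts the whole baseline value, including the noise of a self-reported measure, whatever the actual correlation between baseline and follow-up. A chance baseline difference therefore carries into the estimate through regression to the mean. Regression on the baseline value subtracts only the part that predicts follow-up.

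At stake are the credibility of a single primary result and some power in a trial with little to spare.

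**Working it through.** **Inputs from the Sample Size Calculation section.** Mean and SD: "Surinamese women were on the average 1852 (SD: 1100) minutes per week physically active". The difference sought is 15% of that mean, so 0.15 × 1852 = 277.8 min/week. Error rate, power and size are given as "one-sided alpha of 0.05, and a power of 80% 180 women in both groups are needed". The SD of 1100 refers to a single time point and is not an SD of change.

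**The plan's own figure.** n per arm = 2 × (1.645 + 0.842)² × (1100/277.8)² ≈ 194, against 180 stated. Power at 180 per arm is 77.4%, not 80%. That mismatch is a separate matter; here it shows only that there is no spare power.

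**Assumptions not in the documents.** These are the correlation r between T0 and follow-up, shown at 0.3, 0.5 and 0.7, and, to begin with, equal SDs of 1100 at both times with no dropout.

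**Formulas.**
- SD of change = 1100 × √(2(1 − r))
- Residual SD after baseline adjustment = 1100 × √(1 − r²)
- Variance ratio, adjusted to change = (1 − r²) / (2(1 − r)) = (1 + r)/2, which is at most 1
- One-sided power = Φ(277.8 / (SD × √(2/180)) − 1.645)

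Worked case, r = 0.3. SD of change = 1100 × √1.4 ≈ 1302, and 277.8/(1302 × 0.1054) − 1.645 ≈ 0.38, so power is 65%. Adjusted SD = 1100 × √0.91 ≈ 1049, and 277.8/(1049 × 0.1054) − 1.645 ≈ 0.87, so power is 81%.

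| r | SD change | SD adjusted | Variance ratio | One-sided power, change → adjusted | Two-sided power, change → adjusted |
|---|---|---|---|---|---|
| 0.3 | 1302 | 1049 | 0.65 | 64.8% → 80.7% | 52.6% → 70.9% |
| 0.5 | 1100 | 953 | 0.75 | 77.4% → 86.9% | 66.9% → 79.0% |
| 0.7 | 852 | 786 | 0.85 | 92.6% → 95.6% | 87.1% → 91.8% |

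With equal SDs, 1100 is the right SD for a change only at r = 0.5. Below that, the planned test is weaker than comparing follow-up values with baseline ignored (64.8% against 77.4% at r = 0.3, one-sided).

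**Unequal SDs.** Let k = SD at T0 / SD at follow-up. In units of the follow-up variance, the change score has variance 1 + k² − 2rk and the adjusted analysis 1 − r². The difference is (k − r)², which is never negative and is zero when k = r. At r = 0.5:
- k = 1: 0.75/1.00 = 0.75
- k = 0.7: 0.75/0.79 = 0.95
- k = 0.5: 0.75/0.75 = 1, so no gain

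**How far apart the two estimates can be.** With equal SDs, the change-score and adjusted estimates differ by (1 − r) times the observed baseline difference. One standard error of a chance baseline difference is 1100 × √(2/180) ≈ 116 min. The two estimates then differ by 0.7 × 116 ≈ 81, 0.5 × 116 = 58 or 0.3 × 116 ≈ 35 min at r = 0.3, 0.5 or 0.7. That is 29%, 21% or 13% of the 277.8-min target.

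**The case against.** Under valid randomisation a t-test on change is unbiased, and it does use each woman's baseline, so preferring ANCOVA is partly a question of efficiency. That stands, but it does not answer the undefined trigger for adjustment.

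The size of the gain is uncertain. The SD of 1100 comes from Surinamese women in another study, whereas this trial enrols only insufficiently active women, so a narrower SD at T0 is plausible and the gains in the table could be well too large. This also stands.

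A reader might infer more than the documents support:

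- **That adjustment recovers most of the lost power.** No r is given. Two-sided power after adjustment is still 70.9% at r = 0.3 and 79.0% at r = 0.5. With an assumed 20% dropout, one-sided adjusted power is 72.6% and 79.7% at those values. At r = 0.7 the planned test already exceeds 80%.
- **That women without a follow-up visit will be dropped.** The section states intention-to-treat and does not describe the handling of missing data, which an article may leave to a fuller document.
- **That the baseline comparison should go.** Allocation precedes consent. Controls enter through an opt-out letter, and intervention women through a GP visit, referral and intake (Study Design; Participants and Recruitment). Describing comparability is useful in this design; only its use as a trigger is at fault.
- **That adjustment cures a post-allocation baseline, or that T0 could be moved by rewording.** T0 follows the intake, and intervention women are asked to take part only after it. Adjustment does not remove the resulting selection bias, and the change-score and adjusted analyses may then estimate different quantities. Moving T0 would alter consent and data collection.

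**Conclusion.** The point holds as a matter of prespecification and efficiency. The article fixes an unadjusted change-score t-test for its main aim and leaves adjustment to an undefined judgement after baseline data are seen. A chance baseline difference of one standard error would separate the two candidate estimates by about 35 to 81 min/week (r = 0.7 to 0.3, equal SDs).

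On precision, adjustment for the baseline value of the outcome is never worse in large samples. Under equal SDs of 1100 the gain in one-sided power is about 16, 10 and 3 percentage points at r = 0.3, 0.5 and 0.7. It falls if the baseline SD is smaller than the follow-up SD, and to nothing where the SD ratio equals r. Both r and that ratio are assumptions, so the direction is secure and the size is not. The large-sample result concerns the baseline value of the outcome, not arbitrary covariates.

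**What to change.** Prespecify as the primary analysis a linear model (ANCOVA) for SQUASH minutes per week at T1, and likewise at T2, with arm and T0 SQUASH minutes as terms. Name any further covariates in advance, and report the adjusted differences with 95% confidence intervals. An unadjusted comparison can be kept if it is labelled supportive.

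Delete the clause that makes adjustment conditional. Keep the baseline table as description only, neither as a check on whether randomisation succeeded nor as a trigger for adjustment.

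The cost is a few sentences in Data Analyses. T0 SQUASH minutes are already to be collected in both arms, so no new data, visits or participants are needed. The change should be made and dated before outcome data are compared by arm.
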